**Methods:**

We are conducting a dual centre, randomised, double-blind, placebo-controlled, parallel group trial in northern Australia. Indigenous infants (aged ≤ 24-months, expected number = 200) admitted to one of two regional hospitals (Darwin, Northern Territory and Townsville, Queensland) with a clinical diagnosis of bronchiolitis and fulfilling inclusion criteria are randomised (allocation concealed) to either azithromycin (30 mg/kg/dose) or placebo administered once weekly for three doses. Clinical data are recorded twice daily and nasopharyngeal swab are collected at enrolment and at the time of discharge from hospital. Primary outcomes are 'length of oxygen requirement' and 'duration of stay,' the latter based upon being judged as 'ready for respiratory discharge'. The main secondary outcome is readmission for a respiratory illness within 6-months of leaving hospital. Descriptive virological and bacteriological (including development of antibiotic resistance) data from nasopharyngeal samples will also be reported.

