### Aims of the study

Our primary research question is: Amongst hospitalised Indigenous infants with bronchiolitis, does azithromycin (compared to placebo) improve clinical outcomes (length of stay in hospital and duration of oxygen supplementation)? Our primary hypothesis is that: The anti-microbial and anti-inflammatory properties of the macrolide, azithromycin, will improve the clinical outcomes of Indigenous infants hospitalised with bronchiolitis.

Our secondary aims are:

2. To determine the effect of azithromycin on readmissions into hospital within 6 months of treatment;

3. To assess the short-term impact of azithromycin on macrolide resistance patterns of respiratory bacterial pathogens in the nasopharynx; and

4. To describe the point prevalence and diversity of respiratory viruses, *Mycoplasma pneumoniae *and Chlamydia species using sensitive molecular diagnostic techniques.

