### Sample size

We plan to enrol 200 Indigenous infants. In our retrospective study,[6] the mean LOS in Indigenous infants with bronchiolitis at RDH was 96 (SD 24) hours. The mean duration of supplemental oxygen requirement in Indigenous infants with bronchiolitis was 36 (SD 14) hours. For a mean difference of 24-hours in LOS between groups (power = 90%, α = 5%) the required sample size is 23 per group. The numbers to detect a 12-hour difference in supplemental oxygen requirement is 30 per group. These are large effect sizes but more conservative estimates than seen in the Turkish study[26]. In that study,[26] the difference between groups was 30-hrs for LOS and 31-hours for supplemental oxygen requirement. Assuming similar effects, a sample size of at least 100 in each sub-age group is also sufficient for an *a-priori *subgroup analysis based on age (power of 90% and 2-tailed α of 5%). If the effects are smaller, we will have an 80% power to detect a difference of 10-hours in LOS in all infants and an 80% power to detect a difference of 14-hours in LOS in the ≤6-months age group. We do not believe that smaller benefits than this would be sufficient to change clinical practice.

For the most important secondary outcome (readmission rate for a respiratory illness within 6-months of discharge), the power of our study to detect a reduction from 30% to 10% is 95% (5% significance). This is a large effect but consistent with the reduction described in the Turkish study (75% reduction)[26]. At 80% power we will be able to detect a reduction in readmission rates from 30% to 13%. For our other secondary outcomes, accurate sample size estimations are not possible given the lack of any relevant data.

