### Statistical analysis and reporting

Data will be reported and presented in accordance with the updated CONSORT criteria[40]. Children will be analysed according to allocation status (regardless of subsequent management). An interim analysis is planned and the data safety and monitoring committee will determine if the study should be ceased should superiority of azithromycin be identified after 70% of sample size is achieved.

The primary outcomes (LOS and duration of supplemental oxygen requirement) will be compared between infants receiving placebo or azithromycin using unpaired Student's T-tests or Mann-Whitney tests (depending on normality of distribution). Although we expect randomisation to equally distribute potential confounding factors between each of the groups, we will examine the distribution of known confounders between groups (eg. birth weight, smoke exposure status in-utero and postnatal, breast feeding, etc). Should baseline data differ between groups, regression will be used to check that the primary outcomes are not affected by this chance finding. An *a-priori *sub-analysis will compare infants aged ≤ 6-months with those aged >6-months.

When examining the efficacy of azithromycin at reducing readmission rate for respiratory illness (Secondary Aim-2), the Odds Ratio (OR) between groups will be calculated. The OR will also be used to compare additional antibiotic use between groups. The number needed to treat (NNT) (for benefit), 95% CI will be described if any significant differences are found. If significant, NNT for harm will be calculated for adverse events. For Secondary Aim-3 (short-term impact of azithromycin on macrolide-resistance of pathogens in NPS cultures): the proportions of children with penicillin-non-susceptible *S. pneumoniae *and macrolide-resistant *H. influenzae *spp and *M. catarrhalis *before and after trial medications will be compared using ORs and 95% CI. Descriptive data will be utilised for Secondary Aim-4 (point prevalence of respiratory viruses and other respiratory pathogens).

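### Two unranked primary outcomes are each sized at the full two-sided 5%, and the protocol does not say whether success needs either or both; if either suffices, the family-wise error exceeds 5%.

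*Protocol article*

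**What the plan says.** The abstract of the protocol article names two primary outcomes joined by a plain conjunction: "Primary outcomes are 'length of oxygen requirement' and 'duration of stay". The Primary outcomes section numbers them (i) LOS and (ii) oxygen duration, without calling one the more important. Under Aims of the study, the primary question is whether azithromycin will "improve clinical outcomes (length of stay in hospital and duration of oxygen supplementation"; the hypothesis that follows speaks of clinical outcomes in the plural and goes no further.

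The Sample size section treats each outcome on its own. For LOS: "the mean LOS in Indigenous infants with bronchiolitis at RDH was 96 (SD 24) hours", and for a 24-hour difference, "power = 90%, α = 5%) the required sample size is 23 per group". For oxygen: "The mean duration of supplemental oxygen requirement in Indigenous infants with bronchiolitis was 36 (SD 14) hours", and "The numbers to detect a 12-hour difference in supplemental oxygen requirement is 30 per group". Alpha is not restated for oxygen. Two-sidedness is stated only for the age subgroup ("power of 90% and 2-tailed α of 5" percent).

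Under Statistical analysis and reporting, "The primary outcomes (LOS and duration of supplemental oxygen requirement) will be compared between infants receiving placebo or azithromycin" by a t-test or a Mann-Whitney test. The article gives no order of testing, no either-or-both rule, no split of alpha and no adjustment.

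**The concern.** Two tests, each at 5%, keep the overall false-positive rate at 5% only under certain success rules. It holds if both outcomes must be significant, or if the second is tested only after the first succeeds. It does not hold if a significant result on either one may be presented as confirming the primary hypothesis, and the text leaves that reading open.

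Two things are at stake. One is the error rate attached to the trial's main claim. The other is how to read a split result, with one outcome significant and the other not. A split is quite possible: LOS also depends on feeding, and randomisation is stratified by whether the infant needs oxygen, so some infants enter without it but still contribute LOS. A rule chosen after the results are known would carry little weight.

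**Working it through.** **Step 1. Reproduce the plan's sample sizes.** Inputs from the Sample size section: LOS difference 24 h, SD 24 h; oxygen difference 12 h, SD 14 h; power 90%.

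Normal approximation: n per group = 2 × (z for alpha + z for power)² × (SD/difference)². At two-sided 5%, 2 × (1.960 + 1.282)² = 21.0.

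- LOS: 21.0 × (24/24)² = 21.0, rounded up to 22.
- Oxygen: 21.0 × (14/12)² = 28.6, rounded up to 29.

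The exact t-test calculation adds about one per group and gives the plan's figures:

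| Alpha per outcome | LOS, n per group | Oxygen, n per group |
|---|---|---|
| Two-sided 5%, t-test | 22.02, so 23 | 29.6, so 30 |
| Two-sided 2.5%, t-test | 26.1, so 27 | 35.1, so 36 |
| One-sided 5%, normal approximation | 18 | 24 |
| Plan | 23 | 30 |

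Of these settings, only two-sided 5% fits both figures. The 5% is therefore stated for LOS and inferred for oxygen, and alpha was not divided between the two.

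**Step 2. Family-wise error if either outcome suffices, single final analysis.**

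- Independent outcomes: 1 − 0.95² = 0.0975, or 9.8%. For two-sided normal tests this is the ceiling.
- Correlated outcomes: 1 − P(|Z1| < 1.96 and |Z2| < 1.96), with Z1 and Z2 bivariate normal. The documents give no correlation, so a range is assumed:

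| Assumed correlation | Family-wise error |
|---|---|
| 0 | 9.8% |
| 0.3 | 9.5% |
| 0.5 | 9.1% |
| 0.7 | 8.3% |
| 0.8 | 7.8% |
| 0.9 | 7.0% |
| 0.95 | 6.5% |

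The Data collection and Primary outcomes sections end LOS only after more than 16 hours off oxygen (or normoxic in air) with adequate feeding. LOS therefore contains the oxygen period, and clearly positive correlations are the plausible ones.

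- False claims of benefit only: with independent outcomes, 1 − 0.975² = 0.049, or 4.9% against a nominal 2.5%. Positive correlation lowers this (3.9% at 0.8).

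**Step 3. Family-wise error if both must be significant.** The chance that both are falsely significant cannot exceed the chance for one, so it is at most 5%. No adjustment is needed.

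**Step 4. Price of an adjustment.** With 200 infants, about 100 per group, t-test power:

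| Quantity | Alpha 5% | Alpha 2.5% (Holm, first step) |
|---|---|---|
| Power for 10 h in LOS | 83% | 75% |
| LOS difference detectable at 80% power | 9.6 h | 10.5 h |
| Power for 24 h in LOS | above 99.9% | above 99.9% |
| Power for 12 h of oxygen | above 99.9% | above 99.9% |

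The protocol claims 80% power for 10 hours in LOS. That holds at 5% but not at 2.5%.

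**The case against.** The strongest reply is that nothing here is stated wrongly. The document is a condensed article, and a test order or multiplicity method is often placed in an analysis plan, which is not shown. The analysis section claims no overall 5% error rate; the 5% comes from the sample size inputs. The primary question joins the two outcomes with a conjunction, which can be read as requiring both, and then nothing is inflated.

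Part of this stands. An unseen plan may contain the rule, and the both-required reading is legitimate. But the article does fix two unranked primary outcomes, a separate test for each, and sample sizes at full alpha for each. Whether one or both must succeed belongs with those choices. It also bears on the stated power, because a later split of alpha would undo the 10-hour claim.

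A reader might infer three stronger things that the documents do not support:

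- *That one significant outcome is declared sufficient.* The text leaves this open and does not say it.
- *That the error rate is 9.8%.* That needs independent outcomes, which the definition of LOS makes implausible. The figure also counts false results against azithromycin, although the hypothesis concerns improvement.
- *That the interim look makes it worse by a known amount.* The article sets no boundary and names no outcome for that look, so any such figure rests on further assumptions and belongs to a different point.

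**Conclusion.** The point holds as an undefined success criterion with a conditional effect on the error rate. If significance on either outcome counts as success, the family-wise error at the final analysis exceeds 5%: about 6.5% to 9% for assumed correlations of 0.95 to 0.5, and never above 9.8%. If both outcomes are required, there is no inflation, but the protocol does not say so.

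This rests on three assumptions: a single analysis, approximately normal test statistics, and two-sided 5% for oxygen as inferred from its sample size. It does not call the number of infants into question for the planned 24-hour and 12-hour effects.

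**What to change.** Before unblinding, add one sentence to Statistical analysis and reporting that states a single rule:

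- **Fixed sequence at two-sided 5%.** For example LOS first, then oxygen only if LOS is significant. This follows the order of the Primary outcomes section, but the choice is the sponsor's, since the abstract lists oxygen first. With LOS first, the LOS power figures are unchanged. The cost is that oxygen cannot be claimed if LOS fails.
- **Holm or Hochberg, if the outcomes are to have equal standing.** The Sample size section should then be restated for Holm's first step: 75% instead of 83% power for 10 hours in LOS, and 10.5 instead of 9.6 hours detectable at 80% power.

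If the intention was always that both must be significant, saying so is enough for error control.

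None of these needs more infants for the planned effects. Each controls the error at 5% for one analysis only, so the interim boundary must be dealt with separately.

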### Randomisation, allocation and blinding

The randomisation sequence was computer generated and used permutated blocks (4 or 6 participants per block). The allocation sequence is concealed at all times throughout the study. The computer generation and allocation were performed by a statistician, external to the study team. Upon enrolment, an infant is assigned to the next number on the appropriate stratified list. Each unique number is assigned to one of the eight treatment alphabets (see below). Treatment groups are stratified by age (≤6 or >6 months), site (Darwin or Townsville) and requirement (yes or no) for oxygen at point of randomisation. The importance of excluding older children and stratifying at the 6 month age group is well described[30,34]. A placebo medication ensures that all children, carers, researchers, hospital staff, and clinic staff are blinded to treatment group until analyses of the data.

The placebo medication has been specifically manufactured by the Institute of Drug Technology (IDT) Australia Limited (Melbourne, Vic) which has a similar taste and colour to azithromycin. The azithromycin medications were repackaged by IDT. Thus both the azithromycin and placebo are in identical opaque bottles and sealed with an aluminium foil. For both, equal volumes of water are added using a syringe and needle by punching the seal.

Eight alphabets (N, O, P, Q, R, S, T, U) were used for the bottles of azithromycin and placebo medications (4 alphabets each). We used multiple alphabets rather than sequential numbers on the bottles to allow storage of extra bottles of trial medications in clinics for the day-7 and day-14 doses. This was necessary in the context of our study setting (children mainly from remote Indigenous communities), to enhance availability and administration of trial medications once the child has been discharged from the hospital.

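### Both primary outcomes are tested without the three randomisation factors; this makes the tests conservative and costs precision, mainly for oxygen duration, by an amount the protocol does not let one fix

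*Protocol article*

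**What the plan says.** All references are to the Protocol article.

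- **Randomisation, allocation and blinding.** The sequence "used permutated blocks (4 or 6 participants per block"), and treatment groups are "stratified by age (≤6 or >6 months), site (Darwin or Townsville) and requirement (yes or no) for oxygen at point of randomisation". That makes 2 × 2 × 2 = 8 strata.
- **Statistical analysis and reporting.** LOS and duration of supplemental oxygen "will be compared between infants receiving placebo or azithromycin using unpaired Student's T-tests or Mann-Whitney tests (depending on normality of distribution"). The only adjustment foreseen is conditional: "Should baseline data differ between groups, regression will be used to check that the primary outcomes are not affected by this chance finding". The examples given there are birth weight, smoke exposure and breast feeding; the stratification factors are not named. The limitations section repeats the condition. The comparison of infants up to and above 6 months is a subgroup analysis, not an adjustment.
- **Sample size.** "We plan to enrol 200 Indigenous infants". "The mean duration of supplemental oxygen requirement in Indigenous infants with bronchiolitis was 36 (SD 14) hours". From these figures, 30 per group is given for a 12 h difference in oxygen duration. For LOS (mean 96, SD 24 h), 23 per group is given for a 24 h difference, and 80% power is claimed for 10 h in all infants.

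**The concern.** Stratified blocks keep the arms balanced on the three factors, so differences between strata hardly contribute to the random error of the treatment contrast. A two-sample test that ignores the strata still counts those differences as error. Its standard error is then too large, its true significance level is below 5%, and power is lost.

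How much this matters depends on how strongly a stratifier predicts the outcome. Here one stratifier is oxygen requirement at randomisation and one primary outcome is oxygen duration. Oxygen need is not an entry criterion, so some enrolled infants may have a duration of 0 h. An outcome with many zeros would probably fail a normality check and be sent to the Mann-Whitney test, which in some settings is much the weaker of the two. The conditional regression does not repair this: factors balanced by design will rarely show the difference that triggers it. What is at stake is a real reduction in oxygen duration reported as no effect, or with an interval wider than it need be.

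**Working it through.** **1. The plan's own figures.** A two-sample t-test at two-sided 5% (noncentral t) gives 90% power for LOS (24 h, SD 24) at 22.02, so 23 per group, and for oxygen (12 h, SD 14) at 29.6, so 30 per group. Both stated figures reproduce.

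**2. Whom does 36 (SD 14) h describe?** If a share z of infants has 0 h and the overall mean is 36, the variance is at least 36² × z/(1−z). Setting this to at most 14² = 196 gives z/(1−z) ≤ 196/1296 = 0.151, so z ≤ 13.1%. The figure therefore describes either a population with few zeros or oxygen users only.

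**3. Variance split for oxygen duration.** Assumed: 100 infants per arm; 36 (SD 14) h in oxygen users; half on oxygen at randomisation; the rest never on it.

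- Within strata: 0.5 × 196 = 98.
- Between strata: 0.5 × 0.5 × 36² = 324.
- Total: 422, SD 20.5 h rather than 14 h.
- True level of the unstratified t-test: 2 × [1 − Φ(1.96/√(98/422))] ≈ 0.00005.

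**4. Power for the planned 12 h effect, same setting.** The mean difference over all infants is 0.5 × 12 = 6 h. Treated users average 24 h, so between-stratum variance in that arm is 0.25 × 24² = 144.

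- *Fixed shift (SD stays 14).* The t-test uses SE = √[(422 + 98 + 144)/100] = 2.58; the true SE is √[(98 + 98)/100] = 1.40. Power ≈ Φ[(6 − 1.96 × 2.58)/1.40] = Φ(0.68) ≈ 75%.
- *Proportional reduction (SD 14 × 24/36 = 9.33, within-stratum variance 43.6).* SE used = √[(422 + 43.6 + 144)/100] = 2.47; true SE = √[(98 + 43.6)/100] = 1.19. Power ≈ Φ[(6 − 1.96 × 2.47)/1.19] = Φ(0.98) ≈ 84%.

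These agree with simulation (200 infants, stratified blocks of 4 or 6, gamma durations in users) and suggest why the simulated figure spans a range.

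**5. Simulated power for 12 h across assumed shares.**

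| Off oxygen at randomisation; later need | t | Mann-Whitney | Adjusted |
|---|---|---|---|
| 50%; none later | 74-82% | 23-29% | about 99% |
| 50%; a quarter of these later | 86-92% | 71-82% | 96-98% |
| 30%; none later | 97-99% | 93-98% | >99% |

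Across all settings tried, the true level of the planned oxygen tests was 0.000 to 0.037. Adjusted or stratified tests stayed at about 0.04 to 0.06.

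**6. LOS.** Assumed: total SD 24 h, half on oxygen, 100 per arm, effect 10 h.

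- *24 h gap between oxygen strata.* Between-stratum variance is 0.25 × 24² = 144, or 25% of 576. True level 2 × [1 − Φ(1.96/√0.75)] = 0.024. The SE used is 24 × √0.02 = 3.39 and the true SE is √(432 × 0.02) = 2.94. Power is Φ[(10 − 1.96 × 3.39)/2.94] ≈ 87% planned, against Φ(10/2.94 − 1.96) ≈ 92% adjusted.
- *12 h gap.* The same formulas give a level of 0.043 and power of 85% against 86%.

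**The case against.** The premise that drives the large losses is not in the document. Neither the share of infants off oxygen at randomisation nor their later course is given. Under Recruitment, oxygen is prescribed whenever saturation falls below a threshold, so an infant in the no-oxygen stratum may need it later; enrolment up to 24 hours after presentation means some may have had it before. A reader might infer that the outcome is zero by construction in one stratum. The text does not say so, and later oxygen use shrinks the loss.

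The one documented figure can also be read the other way. Taken literally, 36 (SD 14) h describes Indigenous infants with bronchiolitis in general and leaves room for at most 13% zeros. On that reading, simulated power for 12 h is about 100% for both planned tests. Much larger gaps appear for smaller effects: for 6 h with 70% on oxygen and none needing it later, 27% (t) and 25% (Mann-Whitney) against 77% adjusted. But 6 h is not an effect the protocol plans for.

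Finally, the error is on the safe side, the conditional regression is a check and does not replace the primary test, and an analysis plan that is not shown may adjust for the strata.

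These points limit the size, and they stand. They do not remove the mismatch: the article names an unstratified primary test, and in every simulated setting with a no-oxygen stratum that test was conservative for oxygen duration.

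**Conclusion.** The point holds as one of efficiency. The stated primary tests ignore the factors used to randomise, so they are conservative and less precise than the design allows. For oxygen duration the cost at the planned 12 h effect runs from almost nothing (30% or fewer never needing oxygen) to severe (half never needing it, especially with Mann-Whitney). The document does not show where the trial lies in that range. All these figures assume 36 (SD 14) h in oxygen users.

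For LOS the cost is modest: about 5 points of power under an assumed 24 h stratum gap and 1-2 points under 12 h. The planned test still exceeds the 80% the protocol claims for 10 h.

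Three stronger readings are not supported. Nothing here inflates false positives or biases the estimate. The trial is not shown to be underpowered on both outcomes. The figure of 30 per group is not shown to be wrong: it reproduces, and even with half the infants on oxygen, 200 would give about 50 users per arm. What is unclear is only which infants that figure covers. This should be fixed, but it does not threaten the validity of the trial.

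**What to change.** In Statistical analysis and reporting, replace the normality-dependent choice of test by one pre-specified primary analysis for each outcome: a linear model with treatment, age group, site and oxygen requirement at randomisation, fitted whatever the observed balance, giving a mean difference and confidence interval with robust or bootstrap standard errors. Name a van Elteren test (Wilcoxon stratified by the randomisation strata) as a sensitivity analysis for oxygen duration, with the linear model remaining the primary result if the two differ. Regression on other baseline factors can stay as a secondary check.

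In Sample size, state whether 36 (SD 14) h and 30 per group refer to all infants or to oxygen users; if users, label them so.

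The cost is wording only. The three factors are already recorded for randomisation, and no further infants or data are needed.

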### Intervention and follow up

If eligibility is fulfilled and after informed consent has been obtained, the infant is randomised to receive either a single, oral liquid dose of azithromycin syrup (30 mg per kg) or an equivalent volume of placebo. Medication is given within 24-hours of hospitalisation. Infants randomised to the intervention arm of the study will receive additional treatment doses of azithromycin syrup (30 mg per kg) on day-7 and day-14. Those randomised to the control arm receive an equivalent volume of the placebo syrup. The later doses will be either supervised by study nurses or administered by families with phone support on the day the medication is due. Final clinical follow up will occur in the local health clinic on day-21 (or closest available date from day 20 to 24).

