### Specimen collection

A single nasopharyngeal swab (NPS) specimen for respiratory virus and other potentially important respiratory pathogen (*M. pneumoniae, Chlamydia *spp) testing is collected from each subject at enrolment. In addition, NPS is repeated before hospital discharge for bacterial culture and antibiotic susceptibility testing, as per our laboratory research protocol (see below)[35,36].

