#### Secondary clinical outcomes

The major secondary outcome is readmission for respiratory illness (within 6-months of discharge from hospital). Minor outcomes during hospitalisation: clinical severity score,[27] additional use of antibiotics, and episodes of suppurative otitis media and development of pneumonia. The Day-21 outcomes are: presence of cough, wheeze, abnormal auscultatory chest signs and suppurative otitis media. We will also analyse all clinical outcomes in the following pre-determined sub-groups: (i) age ≤ 6-months; and (ii) presence of bacterial respiratory pathogens that are resistant to macrolide antibiotics.

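### The age sub-analysis is worded as a comparison of ages rather than of treatment effects by age, and the macrolide-resistance subgroup does not say which swab defines it

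*Protocol article*

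**What the plan says.** **Age.** Three sections of the protocol article describe the age analysis.

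- Statistical analysis and reporting: an a-priori "sub-analysis will compare infants aged ≤ 6-months with those aged >6-months". Neither treatment arm is mentioned in that sentence.
- Secondary clinical outcomes: "We will also analyse all clinical outcomes in the following pre-determined sub-groups: (i) age ≤ 6-months". This is an analysis inside one age group; the older group is not listed.
- Sample size: at least 100 infants in each age group are called sufficient at 90% power if effects resemble those assumed, and for smaller effects the trial is said to have "80% power to detect a difference of 14-hours in LOS in the ≤6-months age group". Total enrolment is 200.

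**Resistance.** The second subgroup under Secondary clinical outcomes is "presence of bacterial respiratory pathogens that are resistant to macrolide antibiotics", with no time point. Specimen collection describes the enrolment sample as "A single nasopharyngeal swab (NPS) specimen for respiratory virus and other potentially important respiratory pathogen" testing, and then says that "NPS is repeated before hospital discharge for bacterial culture and antibiotic susceptibility testing". Intervention and follow up adds: "Medication is given within 24-hours of hospitalisation". One of the secondary aims is "To assess the short-term impact of azithromycin on macrolide resistance patterns of respiratory bacterial pathogens in the nasopharynx". The statistical section compares resistance before and after trial medication, which implies a pre-treatment culture as well.

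**The concern.** Age is a real scientific question in this trial. The Background notes that the two conflicting macrolide trials differed in the ages they enrolled, and randomisation is stratified at 6 months. Yet the one sentence that states the age analysis asks whether younger and older infants differ, not whether the benefit of azithromycin differs between them. If analysts instead test treatment separately in each group, significance in one and not the other invites a claim of differential effect that nobody has estimated.

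The resistance subgroup raises a different problem. If it is defined from a swab taken after dosing, membership may itself be a result of treatment. Infants classed as carrying resistant organisms would then not be comparable between arms, and the randomised comparison inside that subgroup would be lost. The timing of a discharge swab also depends on how long the infant stays, which is closely related to a primary outcome.

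**Working it through.** **Inputs (Sample size section).** N = 200; LOS SD 24 h; oxygen duration SD 14 h; two-sided 5%. Equal allocation is assumed (blocks of 4 or 6, four bottle letters per arm). An even age split gives 50 infants per arm in each age group.

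**1. Reproduce the plan's figures.** A two-sample t-test at 90% power needs 23 per group for 24 h in LOS and 30 per group for 12 h in oxygen duration. Both match the article. The detectable LOS difference at 80% power is (1.960 + 0.842) × SD × √(2/n per arm):

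- all infants, n = 100: 2.802 × 24 × √(2/100) = 9.5 h (article: 10 h)
- ≤6 months, n = 50: 2.802 × 24 × √(2/50) = 13.4 h (article: 14 h)

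Both stated values are consistent with rounding up to whole hours. Exactly 80% power for 14 h needs 47 per arm (normal approximation) or 48 (t-based), so 94 to 96 infants aged ≤6 months. With 50 per arm, power within an age group is 99.9% for 24 h in LOS and 99% for 12 h in oxygen duration.

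**2. Dependence on the age split.** At least 100 in each of two groups out of 200 means exactly 100 and 100. Stratification balances arms within age groups but does not fix the size of the groups, and no quota is stated. The age mix is not given, so these shares are assumptions:

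| Share aged ≤6 months | Per arm | Detectable LOS difference, 80% power |
|---|---|---|
| 30% | 30 | 17.4 h |
| 40% | 40 | 15.0 h |
| 50% | 50 | 13.4 h |
| 60% | 60 | 12.3 h |

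The 14-hour figure is optimistic below about 47% and conservative above it (94/200 = 47%).

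**3. The contrast that answers the age question.** The difference between two age-specific treatment effects has SE = SD × √(4/n per cell). For LOS with 50 per cell: 24 × √(4/50) = 6.79 h.

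- 80% power: 2.802 × 6.79 = 19.0 h
- Power for 10 h: Φ(10/6.79 − 1.96) = 31%
- Power for 14 h: Φ(14/6.79 − 1.96) = 54%
- Power for 24 h: Φ(24/6.79 − 1.96) = 94%

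For oxygen duration, SE = 14 × √(4/50) = 3.96 h; the 80% figure is 11.1 h, and power for 12 h is 86%. With an assumed 140/60 age split, the LOS figure at 80% rises to 20.8 h.

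**4. The resistance subgroup, section against section.** The outcomes section defines it by resistant organisms without naming a swab. Specimen collection expressly names only the discharge swab for culture and susceptibility. The first dose is due within 24 hours of hospitalisation, so that swab normally follows it. A secondary aim exists because azithromycin may alter resistance. The statistical section's before-and-after comparison requires a pre-dose culture that Specimen collection does not mention. The text therefore allows either swab, and one of the two is affected by treatment.

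**The case against.** The strongest reply is that the age sentence is merely loose. It closes a paragraph that opens with placebo versus azithromycin, allocation is stratified by age, and both the outcomes and sample size sections point to treatment comparisons inside the age groups. This stands to a degree: a reader might infer that the whole plan tests age instead of treatment, and the documents do not support that. What remains is that the sentence defining the analysis states a different contrast from the other two sections.

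A reader might also infer that the sample size is wrong because it does not power an interaction. It is not wrong. The figures reproduce for the within-group effect, and no section claims power for an interaction. At the size of the main design effect, 24 h, an interaction would even be well powered. The claim that 100 per age group suffices is safe too: by the article's own 23 and 30 per arm, 60 infants in an age group would do.

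The absence of an interaction test, a multiplicity rule or an exploratory label could be made good in an analysis plan that is not shown, and is no fault in itself. Nor can a false-positive rate be had by treating every outcome in both subgroups as an independent test: the outcomes are plausibly correlated and the subgroups overlap.

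On resistance, the before-and-after comparison shows that a pre-treatment culture is intended, and the abstract places swabs at both enrolment and discharge. The documents therefore do not say that the discharge swab defines the subgroup. They leave it possible.

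**Conclusion.** The point holds as a correction to two stated subgroup analyses. The primary comparison is unaffected.

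First, the age sentence names a non-randomised contrast that conflicts with two other sections. If it is meant as a comparison of treatment effects, the trial can detect only large differences: about 19 h in LOS at 80% power. An interaction of 14 h, the size that the article treats as worth detecting in the younger group, would be missed 46% of the time (100% − 54%). These figures assume SD 24 h in every cell, equal allocation and an even age split.

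Second, the 14-hour figure is correct for what it measures but needs its label and its assumption: a within-group effect with about 47 to 50 infants per arm.

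Third, the resistance subgroup is open to selection after randomisation until the swab is named. That bias is possible rather than established, and no size can be put on it from the documents.

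**What to change.** 1. **Statistical analysis and reporting:** replace the age sentence with azithromycin versus placebo within each age group (≤6 and >6 months), each with effect and 95% CI, plus a treatment-by-age-group interaction estimate with 95% CI for LOS and oxygen duration. The planned Mann-Whitney fallback yields no interaction estimate, so take it from a regression model. Align Secondary clinical outcomes with this.
2. **Sample size:** say that the 14-hour figure is the treatment effect within the ≤6-month group and assumes a near-even age split. Add that the interaction has 80% power only for about 19 h under that split.
3. **Secondary clinical outcomes:** define the resistance subgroup by culture of the enrolment swab only, taken before the first dose. State in Specimen collection that this swab is cultured and tested for susceptibility, so that it agrees with the before-and-after comparison.

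Items 1 and 2 cost only wording, though the stated reach of the age analysis becomes more modest. Item 3 costs culture of stored enrolment swabs if that is not already being done.
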